## Conceptual framework

The conceptual framework that will guide this study is inspired by Donabedian [33], and highlights the importance of taking into consideration organizational factors that influence PA integration processes and effects, the processes of integration of PAs into clinical teams and the effects of this integration at the clinical and organizational levels (see Fig. 1). Specifically, the organizational factors that will be studied are: 1) the governance and leadership of those who make decisions and implement PAs [34, 35]; 2) the organizational culture, which includes beliefs, values, norms, and behaviors of those who work in the organization [36]; 3) the human, financial, structural, and information resources [37]; and 4) the methods and tools used to implement the PA intervention.

**Fig. 1 Fig1:**
[figure not shown]
Conceptual framework and the 4 objectives

Regarding the integration processes, we are interested in how the PAs are integrated as full-fledged members of the clinical oncology teams and the nature of the meetings between patients and PAs. We will study the potential effects, if any, of the integration of PAs on the health and psychosocial care oncology teams on: 1) the patients (anxiety; depression; quality of life; compliance to treatments and to lifestyle changes; engagement in their care; experience of care; use of the healthcare system); 2) the healthcare teams (relationships with the patients, collaborative practices, knowledge of cancer patients’ needs, work satisfaction); 3) the administrators and decision makers (how to integrate PA into clinical oncology teams); 4) the PAs themselves (give their story meaning, feeling of usefulness); and 5) the clinical organizational of care .

## Methods/design

### Study design

The planned approach is a longitudinal multiple in-depth case study with two levels of analysis (clinical and organizational) that will be conducted over 4 years at six different sites. The longitudinal design is necessary to account for inevitable delays over the course of the implementation, to allow the time to consolidate changes made at each case site, and to allow the time needed to avoid making premature conclusions regarding the impacts of the changes [38, 39]. The multiple case study design allows for the in-depth analysis of the implementation processes in diverse oncology contexts. Qualitative and quantitative data will be used to document the intervention for each case, to examine the implementation processes, in their respective contexts, and to report their respective effects at the clinical and organizational levels [40]. This design is consistent with realistic evaluation [30] and intervention action-research [29] and structures our in-depth investigation of the links between the implementation and co-construction mechanisms and our ability to capture the challenges and the effects of the intervention.

### Settings

The settings for the cases are six health care organizations in different regions of Quebec: three university hospital centers (Centres Hospitaliers Universitaires) (CHU) and three regional health and social services authorities (Centres intégrés universitaires de santé et services sociaux) (CIUSSS). They were selected based on their interest in integrating PAs into a health and social care oncology team and their capacity to support care partnerships [41]. Specifically, in each setting the PA will be able to: 1) participate in therapeutic education activities about treatments and living with disease (education); 2) offer individualized support to oncology patients in conjunction with the clinical team (emotional); 3) help patients to be more involved in their care (e.g., participate in carrying out their personal action plan) (partnership). The patients selected to be PAs will be clinically stable, receive training (e.g., Knowing the limits of PA role, Communicating and listening, etc.), and will go to the care sites, several hours per week or per month to participate in the above-mentioned education, emotional, and partnership activities.

### Governance

Each site will assemble a local project committee made up of PAs, oncologists, administrators, nurses, oncology nurse coordinators, allied health professionals (e.g., social worker or psychologist), and a research assistant. An overarching study committee comprising the research coordinator for all sites, the research assistants of each site, and an administrator/clinician representative from each site will be in charge of setting up the PA program, discussing challenges and finding solutions, and facilitating the assessment. A community of practice of approximately 30 PAs (between 3 to 5 PAs will be recruited per site) will be formed so the PAs can share successes and challenges and learn from one another. Finally, a steering committee made up of the decision makers and researchers will meet annually to discuss the progress of the project, provide advice on how to carry out the research and comment on the results, and an advisory committee made up of the site representatives (the research assistant and the administrator or clinician) and researchers will review and interpret results of each phase of the study.

### Participants

For each setting, the representatives of high/mid-level managers working in the targeted program, the health and social care professional (HSP) team members, the patients, and the PAs (to be recruited) will be invited to participate in the project. For the patients, the inclusion criteria will be understanding written and spoken French, undergoing cancer screening or treatment, being at least 18 years old and have had at least one meeting with a patient advisor. All participants meeting the inclusion criteria will be invited to participate. This is therefore a consecutive sampling. Professionals and patient advisors will be approached by email. Patients will be approached by telephone or face-to-face through the patient advisor at their initial meeting. All participants will sign an informed consent form approved by Centre Hospitalier de l’Université de Montréal’s research ethics committee. Indeed, this study was submitted to and approved by the Centre Hospitalier de l’Université de Montréal’s research ethics committee.

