### Quantitative data collection

Quantitative data collected will help to achieve the second and third objectives. Validated questionnaires will be used to collect data from each stakeholder group. A summary of the data collection timing and frequency is presented in Table 1. The secure online platform REDCAP (Research Electronic Data Capture), an application for building and managing online surveys and databases, will be used to administer the questionnaires, organize the data collection and analyze the data [52].

**Table 1 Tab1:** List and description of quantitative data collection questionnaires

Outcomes	Questionnaires	Dimensions	Number of items	Response scale	Time of measurements	Question numbers in appendices
**Patient reported experience**	Patient’s care experience questionnaire ^a^	• Site of diagnosed cancer; cancer stage at time of diagnosis; type of treatment; date of start of treatments • Consultation in oncogenetics, genetic status, time of disclosure of results of genetic testing, surgery to reduce the risk of developing cancer, time of preventive surgery • Evaluation of information communicated by medical team, support of friends and family.	25 items	Varied	T0	Additional file 4: T0: 41 to 67
	Sociodemographic questionnaire ^a^	• Gender, age, country of origin, region, number of people in the household, number of dependents, family composition, level of education, perception of financial situation.	18 items	Varied	T0	Additional file 4: T0: 22 to 39
	Patient’s experience with PAs questionnaire ^a^	• Topics discussed, benefits and perceived contribution of PA • Expectations of patients that did not benefit from PA accompaniment	14 items	Varied	T0, T1, T2	Additional file 4: T0: 69 to 100 T1: same as T0 T2: 102 to 127
	Treatment adherence questionnaire [47]	• Intention of receiving treatments • Obstacles to treatment	8 items	5 point Likert scale (1 = strongly disagree and 5 = strongly agree)	T0, T1, T2	Additional file 4: T0: 148 to 159 T1: same as T0 T2: same as T0
	CASE [48]	**Ability to cope with cancer** • Understand and participate in care • Maintain positive attitude • Seek and obtain information	12 items	4 point Likert scale (1 = strongly disagree and 4 = strongly agree)	T0, T1, T2	Additional file 4: T0: 129 to 140 T1: same as T0 T2: same as T0

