#### Questionnaires for patients

Measurements will be taken before the meeting with the PA (T0), immediately following this meeting (T1), and again 1 month after this meeting (T2). Two of the questionnaires used will be co-constructed with patients specifically for this study and assess: patients’ care experience (Additional file 4, questions 41 to 67) and patients’ experience with PAs (Additional file 4: questions 69 to 100 and 102 to 127), following the procedures and sequence of content validation outlined by Haynes and colleagues (1995) [53]. Three validated questionnaires will be used to assess patients’ psychological distress (K6) [49] (Additional file 4: questions 141 to 146), treatment adherence [47] (Additional file 4: questions 148 to 159), and ability to cope with cancer (CASE) [48] (Additional file 4: questions 129 to 140). Data variables of patients’ sociodemographic and clinical characteristics will be collected including sex, age, and type of cancer (Additional file 4, questions 22 to 39). To obtain a complete data set for 30 to 50 patients per site and based on a previously established response rate of 70% [54, 55], we will plan to recruit at least 40 to 70 patients from each site.

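### Eligibility and approach rules conflict with a T0 taken before the patient advisor meeting, so a pre-intervention patient baseline is not assured

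*Protocol article*

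**What the plan says.** All places are in the protocol article.

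- **Participants, eligibility.** Besides language and cancer screening or treatment, patients must meet the criterion "being at least 18 years old and have had at least one meeting with a patient advisor".
- **Participants, invitation.** "All participants meeting the inclusion criteria will be invited to participate". The criteria are thus met first and the invitation follows.
- **Participants, approach.** "Patients will be approached by telephone or face-to-face through the patient advisor at their initial meeting".
- **Participants, consent.** "All participants will sign an informed consent form approved by Centre Hospitalier de l’Université de Montréal’s research ethics committee". No time relative to the first PA meeting is given.
- **Questionnaires for patients.** The timing rule reads: "Measurements will be taken before the meeting with the PA (T0), immediately following this meeting (T1), and again 1 month after this meeting (T2").
- **Table 1, patient's experience with PAs questionnaire.** It is scheduled at T0, T1 and T2, with the same items at T0 and T1 (questions 69 to 100) and another block at T2 (102 to 127). Its content is described in two bullets. The first is "Topics discussed, benefits and perceived contribution of PA"; the second, for a different group, is "Expectations of patients that did not benefit from PA accompaniment".

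**The concern.** A patient who qualifies only by having met a PA, and who is approached through the PA at that meeting, has no obvious opportunity to give consent and complete questionnaires before it. Yet T0 is defined as exactly that measurement.

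K6, CASE and treatment adherence are each measured at T0, T1 and T2. The article describes no comparison group of patients, so T0 is the only reference against which change can be read. If T0 is taken once PA contact has begun, the changes to T1 and T2 leave out whatever had already happened. These changes are the quantitative patient part of objective 3, and the results are also meant to help design a later randomized trial. A baseline missed before exposure cannot be recovered afterwards.

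**Working it through.** The protocol has no figure to reproduce here; the check is one of sequence.

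**Order of events under each reading of the meeting that defines T0**

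1. *It is the first PA meeting.* T0 comes before any PA contact. At that moment the patient has had no PA meeting, so the eligibility rule is not met, and the invitation is restricted to those who meet it. No patient is eligible at T0.
2. *It is a later meeting.* The eligibility rule is met. T0 precedes that later meeting but follows at least one earlier PA contact. T0 to T1 then measures what the later meeting adds, not change from first contact.
3. *T0 comes first and inclusion is confirmed once the first meeting has taken place.* T0 is pre-intervention. The article does not state this sequence, and its order of meeting the criteria and then being invited runs the other way. It would also leave out patients who completed T0 but never met a PA.

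Only reading 3 gives the baseline the analysis needs, and nothing in the text tells a site to follow it.

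**Does Table 1 settle it?** No. Items on what was discussed with the PA and what the PA contributed presuppose a past meeting, yet they are listed at T0. The bullet on expectations concerns patients without PA accompaniment, which suits a T0 before any contact but describes people the eligibility rule would exclude. The cell points both ways.

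**Direction and range of the effect.** Suppose all change is due to PA contact. Let D be the true change from before first contact to the follow-up time, f the fraction of T0 forms completed after first contact, and s the share of D already present in those forms. Then

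observed mean change = (1 − f) × D + f × (1 − s) × D = D × (1 − f × s).

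- Reading 3: f = 0, so the observed change is D.
- Reading 2: f = 1, so the observed change is D × (1 − s). This is D if s = 0 and zero if s = 1.

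With f and s each between 0 and 1, the observed change runs from D down to zero. The share s may differ between T1 and T2: if effects build over the month, less of the T2 change is lost. The protocol gives no value for D, f or s, so the range cannot be narrowed.

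**The case against.** The strongest reply is that the T0 definition is as literal as the eligibility rule, so there is no reason to let the second override the first. The authors may well have intended a true pre-meeting T0. A telephone approach is allowed and could precede the meeting. An article may also leave the exact moment of consent to the full protocol. All of this stands as far as intention goes. It does not reconcile the text: the approach is still tied to the PA and the initial meeting. Under Study challenges and mitigation strategies, teleconsultation is offered in place of the PA's physical presence, so a call may itself be the first contact. At best, exposure at T0 would vary with the mode of approach, with no rule to control it.

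On Table 1, the reply is right that a patient with no PA contact could answer the expectations items. The advisors' own version of this questionnaire asks whether a pairing took place, which suggests branching. Additional file 4 is not shown, so the items actually presented at T0 cannot be judged. Table 1 therefore adds ambiguity; it does not prove that T0 is late.

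It is also fair that this is a feasibility case study looking for effects, if any, and that without a comparison group even a sound T0 would not attribute change to PAs. But describing change at all requires knowing what it is measured from.

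**Conclusion.** The point holds as an inconsistency between current statements that must be reconciled before patients are enrolled. The eligibility criterion, the approach and the T0 definition cannot all be followed as written unless an unstated sequence is assumed. A pre-intervention baseline is therefore not assured, and the T0–T1 and T0–T2 changes in K6, CASE and adherence may understate or miss change from first PA contact. This rests on there being no patient comparison group, and none is described. The size cannot be given from the protocol.

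Two stronger conclusions might be inferred, and the documents do not support either:

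- *Every T0 is taken after exposure, so the immediate contrast is zero.* This gives the eligibility sentence full force and the equally explicit T0 definition none. It also ignores the telephone route. Even under reading 2 the contrast is zero only if the whole effect is already present at T0. Any stated loss of effect or power would need an effect size, and the protocol has none; its 30 to 50 patients per site is a target for complete data.
- *Objective 3 cannot be answered for patients.* The article also serves that objective with qualitative data: interviews, focus groups that include patients, and the research logbook. Only the quantitative change scores are at risk.

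**What to change.** 1. In Participants, replace the criterion of a meeting already held by: referred to or booked for a first PA meeting, with no earlier PA meeting.
2. Reword the approach sentence so that the site research assistant obtains consent and T0 in REDCap before that meeting.
3. State in Questionnaires for patients that T0, T1 and T2 refer to this first meeting.
4. In Table 1, split the questionnaire on experience with PAs: expectations items only at T0, experience items at T1 and T2.
5. Compare the T0 completion time in REDCap with the meeting date and time in the PA logbook, which Table 1 already plans to record. Leave any T0 completed after the meeting began out of the main change-from-baseline analysis, and report how many there were.

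The cost is an amendment to a few sentences and one table row, plus earlier patient contact by research assistants already planned at each site. Some consented patients will never meet a PA. Their number cannot be predicted from the article, but it is worth reporting in a feasibility study.

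### Patients qualify only after meeting a patient advisor (PA) and are approached at least partly through that PA, so the sample is at best consecutive among acceptors, has no denominator of offers, and does not fit a pre-meeting T0

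*Protocol article*

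**What the plan says.** All references are to the protocol article.

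- **Eligibility (Participants).** Among the patient criteria is "being at least 18 years old and have had at least one meeting with a patient advisor".
- **Route (Participants).** "Patients will be approached by telephone or face-to-face through the patient advisor at their initial meeting". The sentence does not say who makes the telephone approach.
- **Sampling label (Participants).** "All participants meeting the inclusion criteria will be invited to participate. This is therefore a consecutive sampling".
- **Timing (Questionnaires for patients).** The schedule reads: "Measurements will be taken before the meeting with the PA (T0), immediately following this meeting (T1), and again 1 month after this meeting (T2").
- **Content (Quantitative data collection, Table 1).** The questionnaire on patients' experience with PAs is given at T0, T1 and T2. It covers topics discussed and what the PA was felt to bring, and also "Expectations of patients that did not benefit from PA accompaniment".
- **Records (Logbook).** The PA completes an entry after each meeting held. Table 1 lists the patient's name and the date among its fields.
- **Staff (Governance).** Each local committee already includes "allied health professionals (e.g., social worker or psychologist), and a research assistant".
- **Use of results (Background, Abstract, Conclusion).** The study is to judge the feasibility of integrating PAs and to assess effects on patients. Promising results are to lead to a pragmatic randomized trial.

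**The concern.** The person who delivers the intervention is also a route into the sample that judges it. A PA may be less inclined to invite a patient with whom contact was difficult. A patient invited by a PA may feel obliged to answer kindly.

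Separately, patients who were offered a PA and declined, or who never got as far as a meeting, are excluded by rule. They are the people who would say most about acceptability.

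Finally, a patient awaiting a first PA meeting does not yet meet the criterion, although the baseline is meant to be taken at that point.

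At stake are how far the perceived-benefit ratings can be trusted, what the questionnaire data can say about feasibility and acceptability, and whether T0 is a true baseline. All three bear on the decision to go on to a randomized trial.

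**Working it through.** **1. The plan's own patient figure.** Questionnaires for patients aims for 30 to 50 complete data sets per site at 70% response. 30/0.70 = 42.9 and 50/0.70 = 71.4, so 43 to 72 after rounding up, against a stated minimum of 40 to 70. The small gap does not matter here. The point concerns who can enter the sample, not how many.

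**2. Criterion, route and baseline side by side.** Take a patient about to have a first PA meeting.

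| Element | Section | When it applies |
|---|---|---|
| T0 questionnaires | Questionnaires for patients | before the meeting |
| Approach to the patient, at least face-to-face | Participants | at the initial meeting |
| Eligibility satisfied | Participants | after a meeting |

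Read literally, T0 comes before both the approach and eligibility. There are two ways out. If T0 precedes a later meeting, the baseline already follows exposure to a PA. If T0 precedes the first meeting, the patient must be approached earlier and the criterion cannot yet be met. The text does not choose between them.

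**3. What kind of consecutive sample.** If all who satisfy the criteria are invited, the sample is consecutive among patients who met a PA. It is not consecutive among patients offered a PA, nor among the oncology patients of the site.

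**4. How much one PA can weigh.** Governance gives 3 to 5 PAs per site. With 40 to 70 recruits shared equally, each PA is linked to between 40/5 = 8 and 70/3 = 23 patients, that is 1/5 to 1/3 (20% to 33%) of a site's sample. This is the most that one PA could influence under equal shares, and it is less if telephone approaches are made by someone else.

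**5. Illustration of selective entry (assumed values, none from the article).** Let p be the true share perceiving benefit among patients who met a PA, and r the ratio of their chance of entering to that of the others. The observed share is p·r / (p·r + 1 − p). With p = 0.60:

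| r | Calculation | Observed share |
|---|---|---|
| 1 | 0.60/1.00 | 60% (no bias) |
| 1.25 | 0.75/1.15 | 65% |
| 1.5 | 0.90/1.30 | 69% |
| 2 | 1.20/1.60 | 75% |

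**6. Illustration of the missing denominator (assumed values).** The lower target gives 6 × 40 = 240 recruits. If 70% of patients who met a PA enter, 240/0.70 = 343 met one. With uptake of 80%, about 343/0.80 = 429 were offered a PA; with uptake of 20%, about 1,714 were. The same 240 questionnaires fit both. The PA logbook counts meetings held, which is a numerator only.

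**The case against.** Several stronger readings are tempting, and the text does not support them.

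- **That the sampling is not consecutive.** The article says "All participants meeting the inclusion criteria will be invited to participate". Inviting everyone who meets the criteria is consecutive sampling of that group. The label is incomplete rather than false.
- **That the sample favours satisfied patients.** This is a risk, not something the article states. The approach is made at the initial meeting, when satisfaction is largely unknown, and selective invitation would breach the invite-all rule. With equal invitation the bias is zero. Logbook entries could be compared with invitations as a partial check, although the PA writes them.
- **That every patient is recruited by the PA, or that PAs see the answers.** The telephone caller is not clearly identified. Questionnaires run on a secure platform, and nothing says that PAs administer or read them.
- **That uptake will be misreported.** Uptake is not among the four objectives, and feasibility is studied largely through interviews, focus groups, documents and research logbooks. A log of offers may exist in a fuller protocol, so its absence from an article is not in itself a fault.
- **That no eligible patient could answer the Table 1 item on unaccompanied patients.** It may be meant for T0, before the meeting. The item wording is in an additional file that is not shown.

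It is also fair to say that limiting the effects analysis to exposed patients is defensible in exploratory case studies, and that the K6, CASE and adherence scales do not rate the PA.

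These arguments narrow the point but do not remove it. The criterion, the route and the T0 timing are all stated in the article and do not fit together, and the sample they define contains acceptors only.

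**Conclusion.** The point holds in limited form. As written, the patient sample is at best consecutive among those who accepted and met a PA, and it is gathered at least partly through the PA being rated. It supplies no denominator of offers. Gatekeeping and courtesy answers would plausibly push perceived-benefit ratings upward, but the article gives nothing from which to size this. The 60% to 75% range rests wholly on assumed values and includes no bias at its lower end.

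The firmest part needs no assumption. A post-meeting criterion and an approach at the initial meeting conflict with a pre-meeting T0, and they sit uneasily with the Table 1 item on patients without a PA. No figure in the article is overturned. This is an inexpensive improvement to the design and does not invalidate the study.

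**What to change.** 1. Have the existing site research assistant invite and consent all consecutive patients offered or referred to a PA, by telephone or face-to-face, before the first meeting. T0 then becomes workable.
2. Give the PA no role in consent or questionnaires, and state that answers are not visible to the PA.
3. Reword the criterion to patients offered or scheduled for a PA meeting, and keep the effects analysis to those who then meet one.
4. Keep a simple log by site of patients offered, accepted, met, consented and retained, and report the proportions with 95% confidence intervals.
5. Describe the sample as consecutive among patients offered a PA, and say at which time point, and to whom, the Table 1 item on unaccompanied patients applies.

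Following decliners to T2 is optional and not part of this change. It would add a new cohort for which the recruitment target was not set.

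The cost is an amendment of the recruitment wording and some research-assistant time. Consents will exceed the number who meet a PA. For 40 who meet one, 40/0.80 = 50 consented patients are needed if 80% go on to meet, and 40/0.50 = 80 if half do (both assumed). The assistants also run interviews, focus groups and logbooks, so their capacity should be checked. No new instrument is needed.
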